### Assessments

First of all, a standardized printed form will be used that will include personal data (name, age, sex, place of birth, contact telephone number, education, monthly family income, marital status, and occupation) and anthropometric data (height and weight, measured as recommended by the National Institute of Health, Heart, Lung, and Blood) [19]; diagnosis of current illness; preexisting illnesses; current or past smoking history; history of alcohol consumption and medications used; previous chemotherapy or radiotherapy; whether the current chemotherapy is neoadjuvant, adjuvant, treatment of choice, or palliative; and whether the patient is or was a practitioner of physical activity and how often they performed such activity.

The primary outcome will be assessed via frequency and intensity. Discomfort caused by the main adverse symptoms of chemotherapy (such as pain, nausea, and dry mouth) will be assessed using the Memorial Symptom Assessment Scale, Brazilian version (MSAS-BR) [20]. This scale consists of 32 symptoms that are scored by the patient according to their frequency and intensity (1-4 points, with 1 being less intense and frequent) and the discomfort (0-4, zero being no discomfort) that this symptom caused the previous week. This scale gives us a final index, which consists of the average of the 3 domains (frequency, severity, and bother) and all items, in addition to 4 subscales: Psych, which assesses psychological symptoms (with six items); Phys H, which assesses the most prevalent physical symptoms (with 12 items); Phys L, which assesses the less prevalent physical symptoms (with 14 items); and the Global Distress Index, which measures 4 psychological and 6 physical symptoms [20,21]. This scale will be applied in the initial and final assessments by an evaluator blind to which group the patient belongs.

Other outcomes will be assessed, such as fatigue, level of patient mobility, length of hospital stay, and clinical complications. Fatigue will be assessed using the Brief Fatigue Inventory, Brazilian version. This inventory consists of 9 items that are rated from 0 to 10 on a visual numeric scale. The first question is a dichotomous question about whether the patient has felt tired or fatigued in the last 7 days. Three items refer to the severity of fatigue at the time of assessment, the usual fatigue in the last 24 hours, and the worst fatigue in the last 24 hours, where 0 represents no fatigue and 10 “the worst fatigue imaginable.” The other 6 items refer to how fatigue interfered with different aspects of the patient’s life in the last 24 hours; these items are “general activities,” “mood,” “ability to walk,” “work” (including work outside and at home and daily tasks), “relationships with other people,” and “enjoying life,” where 0 means that it does not interfere and 10 means that it interferes completely [22,23]. This inventory will be applied in the initial and final assessments by an evaluator blind to which group the patient belongs.

The level of mobility will be assessed using the De Morton Mobility Index. This scale is made up of 15 activities, where 11 are classified as 0 or 1 (incapable or capable, respectively) and 4 are classified as 0, 1, or 2 (incapable, partial, and capable, respectively). Of the 15 activities, 3 are performed in bed, 3 in a chair, 4 involve static balance, 2 involve walking, and 3 involve dynamic balance. The scale was translated and validated in Brazilian Portuguese [24,25] and ranges from a score of 0, which represents low mobility, to 100, which represents high mobility. This index will be applied by an evaluator who is blind to which group the patient belongs and will be applied in the initial and final assessments.

In addition, the total number of days of hospital stay, possible clinical complications (cardiac, pulmonary, infectious, or neurological) arising from chemotherapy treatment, and the need for transfer to the intensive care unit will be accessed through the medical records of the patient.

The adverse effects of aerobic training, such as muscle pain, will be collected in the form of a question, developed by the researchers themselves, that will be answered every day before starting a new aerobic exercise session. In the same way, the patients’ subjective perception of satisfaction and discomfort in relation to the proposed protocol will be assessed through 2 questions developed by the researchers themselves that will be answered on the day of the patients’ final assessment. The patients’ responses to the questions will be on a scale of 0 to 10. In the question about satisfaction with the treatment, 0 will indicate “complete dissatisfaction” and 10 “maximum satisfaction.” When the question is about the discomfort of the treatment, 0 will indicate “no discomfort” and 10 will indicate “maximum discomfort.”

At the end of the treatment, the acceptability, suitability, and feasibility outcomes will be assessed using the Weiner scale [26], which was translated and adapted into Brazilian Portuguese [27]. The answer options for all questions are “completely disagree” (1 point), “disagree” (2 points), “neither agree nor disagree” (3 points), “agree” (4 points) and “completely agree” (5 points).

Acceptability is the perception among parties interested in implementing a given treatment that it is pleasant or satisfactory. It will be evaluated in terms of patient satisfaction in the intervention group according to their responses to the following statements: (1) “Physical exercise during chemotherapy treatment has my approval”; (2) “Physical exercise during chemotherapy treatment is attractive to me”; (3) “I enjoyed physical exercise during chemotherapy treatment”; and (4) “I recommend physical exercise during chemotherapy treatment.”

As for suitability, it is the relevance or compatibility of the proposed innovation (ie, treatment) for a given clinical practice environment. It will be evaluated by the following statements addressed to health professionals who care for patients included in this study, such as doctors, nurses, and physiotherapists: (1) “Physical exercise during chemotherapy treatment seems appropriate”; (2) “Physical exercise during chemotherapy treatment seems adequate”; (3) “Physical exercise during chemotherapy treatment seems applicable”; and (4) “Physical exercise during chemotherapy treatment seems to be a good option.”

Feasibility is defined as the extent to which a new treatment can be implemented within a given environment. It will be evaluated by the following statements addressed to physiotherapists and patients included in this study: (1) “Physical exercise during chemotherapy treatment seems implementable”; (2) “Physical exercise during chemotherapy treatment seems possible to perform”; (3) “Physical exercise during chemotherapy treatment seems feasible”; and (4) “Physical exercise during chemotherapy treatment seems easy to use.”

Economic evaluation will be monitored during the hospitalization period [28]. The index year will refer to the year of data collection. The costs of the intervention used will be assumed through the estimated value of the instruments used (oximeter and cycle ergometer), as well as the booklets and the in-hospital physiotherapy sessions (using the reference fees from the Physiotherapy Council table). The assessment of health care costs corresponds to the individual’s costs to the health care system and the costs of lost productivity due to total days of hospitalization. This assessment will be carried out using cost information obtained at the hospital. The cost-effectiveness analysis will be carried out by evaluating the effects of the intervention using the MSAS-BR-16 questionnaire, while the cost-utility analysis will be measured by quality-adjusted life years (QALYs) using the quality-of-life questionnaire EQ-5D-3L [29]. Sensitivity analysis will test uncertainty in key parameters, such as selection of cost weights and statistical variation in quality-of-life scores.

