## Abstract

**Background:**

One strategy to prevent adverse effects resulting from chemotherapy treatment is to perform physical exercises during treatment. However, there is still no consensus on the best type and intensity of exercise, nor when it should be started. Most studies have been carried out in patients with breast cancer, usually a few weeks after starting chemotherapy, on an outpatient basis 2 to 3 times a week. The main differences in our study are that we carried out physical training in hospitalized patients undergoing a cycle of chemotherapy for cancer treatment and that this training was carried out 5 times a week and was not restricted to a specific type of cancer.

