### Participants

Patients older than 18 years diagnosed with cancer and hospitalized in the ward to undergo at least 1 cycle of chemotherapy will be eligible for this study. Patients will be included in the study if they do not have musculoskeletal, cognitive, or clinical limitations that interfere with the proposed assessments and interventions, such as heart disease (eg, moderate to severe aortic or pulmonary stenosis, decompensated heart failure, advanced cardiac arrhythmias, myocarditis, and unstable coronary insufficiency), lung diseases (eg, chronic obstructive pulmonary disease or decompensated asthma), diabetes mellitus, and decompensated systemic arterial hypertension with serum hemoglobin <8g/dL or hematocrit <25% or platelets <30,000 mm [5,13-15].

Patients who require transfer to the intensive care unit, or for whom chemotherapy treatment has been contraindicated or discontinued for any reason, will be excluded from the study.

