### Procedures

During the protocol period, all patients admitted to the oncology ward who are identified and meet the eligibility criteria will be invited to participate in the study by the evaluating physiotherapist. These eligible patients will be informed about the objectives of the study and invited to sign the informed consent form. Next, the patients will be evaluated regarding anthropometric and clinical characteristics, fatigue, and mobility, as well as the occurrence, frequency, intensity, and discomfort of the main adverse effects of chemotherapy. After the initial assessment, patients will be randomized into an intervention group, which will perform aerobic exercise sessions, and a control group, which will receive a booklet with guidelines (the same booklet will be given to the patients in the intervention group). The next day, the intervention will begin. Aerobic training will be carried out from Monday to Friday while the patients are hospitalized for the chemotherapy cycle in the oncology ward. Before carrying out the day’s aerobic exercise session, the patients will be asked if they feel any type of discomfort that is related to the previous day’s training (for example, muscle or joint pain in the lower limbs). If for any reason chemotherapy is interrupted for a patient, the exercises will also be interrupted, and as soon as chemotherapy treatment is resumed, the exercise will also be resumed. The booklet will be given to the patients and explained by a trained physiotherapist. Patients will be re-evaluated on the day following the last day of the chemotherapy cycle regarding the occurrence, frequency, intensity, and discomfort of adverse effects of the treatment, as well as fatigue, mobility, and satisfaction with the proposed intervention.

After the study intervention period, patients who need it will receive routine physiotherapeutic care provided by the physiotherapy team at the hospital. The incidence of clinical complications from chemotherapy and the length of hospital stay will be assessed as outcomes until hospital discharge. All data will be collected by a blinded assessor. Additionally, data will be coded and entered into a Microsoft Excel spreadsheet and will be double-checked before analysis. A visual representation of the study design is presented in Figure 1.

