### Randomization

Immediately after baseline assessments and before starting the intervention, patients will be randomly allocated to 1 of 2 groups: intervention or control. The allocation will be conducted by a researcher who will not be involved in the selection or evaluation of patients or in the intervention; it will follow a randomization schedule generated by a website [16] with a 1:1 allocation rate. The rooms in the ward accommodate 2 to 4 patients (beds); therefore, randomization will be carried out by group or cluster [17]. The rooms will be randomized, because although the intervention is directed to one patient, it can affect another patient in the same room, contaminating those who should not receive the intervention and reducing the estimated result [17]. The researcher responsible for randomization will place a written document inside a sealed opaque envelope indicating which group (intervention or control) each room belongs to in order to ensure the confidential allocation of patients to the blinded evaluator [18]. Before starting the intervention, the physiotherapist responsible for the intervention will open the envelope in front of the patient and disclose which group the room the patient is in corresponds to.

Due to the nature of the study, it will not be possible to blind the physiotherapist responsible for the intervention or the patients. However, the evaluator will be blinded to the groups (intervention and control). After the intervention and assessments, the physiotherapist responsible for the intervention will ask the blinded evaluator to which group (intervention or control) he believes each patient belonged to evaluate the evaluator’s blinding.

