### Statistical Design

The calculation to determine the sample size was carried out based on a previous randomized clinical trial that also compared the effect of aerobic training compared to usual care on the deleterious effects of chemotherapy in patients with breast cancer [11]. Our study was designed to detect a difference of 2.7 (SD 4) points in the physical fatigue score, in addition to a difference of 6.2 (SD 7) episodes of vomiting or nausea between the groups. A power of 80%, an α of 5%, and a loss to follow-up of 15% of the sample were considered. A sample of 94 patients (47 patients in each group) was estimated.

After the data collection, all analyses will be conducted following intention-to-treat principles and will be performed by a researcher who will not be involved in the study assessments and intervention.

For analyzing the effect of the intervention, after a descriptive analysis and the Shapiro-Wilk normality test with a visual analysis, the groups will be compared using a linear mixed model for fatigue, mobility, and chemotherapy-related symptoms before and after the intervention. The length of hospital stay will also be compared between groups using Kaplan-Meier survival analysis. The *χ*^2^ test will be used to compare the clinical complication rates between groups. Descriptive analysis will be used for recruitment, completion, and adherence rates and potential adverse events. The significance level will be set at 5%. For all these analyses, SPSS (version 21.0; IBM Corp) will be used.

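### Length of stay is counted as total hospital days and compared without allowance for planned cycle length, which may cost precision on a secondary hypothesis

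*Protocol article*

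**What the plan says.** The Assessments section lists stay among the outcomes other than the primary one and defines it as "the total number of days of hospital stay", read from the medical record. Procedures gives the end point: "The incidence of clinical complications from chemotherapy and the length of hospital stay will be assessed as outcomes until hospital discharge". No starting day is named. Statistical Design gives the analysis: "The length of hospital stay will also be compared between groups using Kaplan-Meier survival analysis". No covariate or stratification is mentioned for it.

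Three other statements bear on what those days contain:

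- Participants are people "hospitalized in the ward to undergo at least 1 cycle of chemotherapy", so treatment days are part of every stay.
- Allocation comes after admission, consent and baseline assessment (Randomization: "Immediately after baseline assessments and before starting the intervention, patients will be randomly allocated to 1 of 2 groups"). Training starts later still (Procedures: "The next day, the intervention will begin").
- The abstract says that the training "was not restricted to a specific type of cancer", so regimens can differ between patients.

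A shorter stay is one of the stated hypotheses in the Introduction. The baseline items listed under Assessments include diagnosis, medications and treatment intent, but not the planned length of the cycle.

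**The concern.** A patient's total stay can be split into three parts: days from admission to randomisation, the remaining scheduled days of the cycle, and any days added by delay or complications. Exercise cannot change the first part. It can change the second only in so far as it alters whether the cycle runs to schedule. The third is where most of any benefit would be expected. The plan adds all three together and compares the sums.

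If the first two parts differ a good deal between patients, they add variation that hides an effect on the third. In a trial of 94 patients with no stratification named, one arm may also by chance receive more patients on long cycles, and nothing in the stated analysis would correct for it. At stake is how informative the result on the stay hypothesis will be. A null result could not easily be told apart from one blurred by regimen mix.

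**Working it through.** **Plan's own figure.** There is none for stay. The sample size rests on fatigue and on vomiting or nausea, and the documents give no mean, SD, regimen length or admission-to-randomisation gap. What follows is therefore an illustration over a range.

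**Inputs.**

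- Patients analysed: 47 per arm less 15% loss (Statistical Design), 47 × 0.85 = 39.95, taken as 40.
- 80% power and 5% alpha (Statistical Design), taken as two-sided, giving a multiplier of 1.96 + 0.84 = 2.8.
- Assumed: SD of stay beyond plan, 2 days.
- Assumed: SD of planned plus pre-randomisation days, 1 to 4 days, uncorrelated with stay beyond plan.
- Assumed: independent patients. Room allocation is ignored here.

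**Formulas.** Total SD = √(2² + SDplanned²). Detectable difference = 2.8 × SD × √(2/40) = 0.626 × SD.

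| SD of planned plus pre-randomisation days | Total SD | Share of variance from those days | Detectable difference (days) |
|---|---|---|---|
| 0 (fully removed) | 2.00 | 0% | 1.25 |
| 1 | 2.24 | 1/5 = 20% | 1.40 |
| 2 | 2.83 | 4/8 = 50% | 1.77 |
| 3 | 3.61 | 9/13 = 69% | 2.26 |
| 4 | 4.47 | 16/20 = 80% | 2.80 |

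**The same point as power.** Suppose the true difference is 1.5 days. Power = Φ(1.5 / (SD × √(2/40)) − 1.96). With SDs of 0, 1, 2, 3 and 5 days for the planned plus pre-randomisation part, power is 92%, 85%, 66%, 46% and 24%. If stay beyond plan has SD 3 instead of 2, the figures are 61%, 56%, 46%, 35% and 21%.

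**Check on the survival scale.** The plan uses Kaplan-Meier, not a comparison of means, so log-rank tests were simulated with 40 per arm and 1,000 runs per setting. The modifiable part was exponential, with mean 3 days in one arm and 1.5 in the other. Power was computed for that part alone and again after adding days unrelated to allocation:

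- a constant 6 days: 83% before, 83% after;
- 3 to 5 days, varying between patients: 85% before, 81% after;
- 2 to 11 days, varying between patients: 86% before, 49% after.

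Both calculations agree. The number of planned days does not matter in itself. Only their spread between patients costs power.

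**The case against.** The strongest reply is that total stay is a legitimate outcome. The objective concerns hospital stay during the treatment cycle, and total stay measures it directly. Days that allocation cannot affect are balanced in expectation between randomised arms, so the between-arm difference still estimates the effect on stay. Chance imbalance is ordinary sampling error, and the 5% test already allows for it. All of this stands, and it limits the point to precision. A reader might infer that the outcome cannot answer the stay objective; the documents do not support that.

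A second reply is that a time origin and covariates for a secondary outcome are details an article may leave to the full protocol or analysis plan, and that counting from admission is an inference from the word total. This stands in part. Their absence alone would be no finding. But the article does fix the measure as total days, and the plain reading of that includes days before randomisation.

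A third reply is that planned length may be recoverable from the diagnosis, the medication data or the prescription in the record. That is fair, and it is why the repair is cheap. It is still better to capture it before allocation is known than to reconstruct it afterwards.

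Finally, total days also feed the lost-productivity costs in the economic evaluation. That is the right quantity for costs and is not a defect.

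**Conclusion.** The point holds as a matter of precision. The stated definition counts pre-randomisation and scheduled treatment days, and the stated analysis does not allow for them. Under the assumptions above, the detectable difference rises from about 1.25 days to between 1.4 and 2.8 days. At the low end of that range the loss is slight. The 1.25-day figure is a best case in which planned days are fully accounted for. The normal approximation, the zero correlation and the independence of patients are all assumptions, and allocation by room could widen every figure.

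Two stronger readings are tempting and go too far. A reader might infer that total stay is dominated by time that exercise cannot change. Nothing in the documents shows this: in the table that share runs from 20% to 80%, depending wholly on an assumed SD. A reader might also infer that each regimen fixes the treatment days. Procedures provides for chemotherapy to be interrupted and resumed, so the days needed to finish a cycle can themselves vary, possibly with the toxicity that exercise is meant to reduce.

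Severity is minor: stay is a secondary outcome, the sample size does not rest on it, and no bias in expectation follows from this definition.

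**What to change.** Define the stay outcome as days from randomisation to discharge. At baseline, before the allocation envelope is opened, record the prescribed last day of the current cycle. Compare arms with an analysis adjusted for planned remaining cycle days, for example a Cox model reported alongside the Kaplan-Meier curves, or a comparison stratified by planned length. Keep total days as a descriptive measure and for costing.

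An outcome counting only days beyond the planned last day is possible but is a matter of preference. It may be zero for many patients, so its precision is uncertain too. Days from randomisation, adjusted for planned length, make use of every patient's stay and capture delays within the cycle.

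The cost is one baseline field taken from the prescription, a changed definition in the text and a slightly more complex analysis. For patients already recruited, the planned last day would have to be taken from the prescription as written at baseline, by someone unaware of allocation.

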### Interventions

The patients allocated to the intervention group will participate in an aerobic training protocol on a cycle ergometer during the period in which they are hospitalized and undergoing the chemotherapy cycle. The training will be carried out with daily sessions for 4 days lasting 40 minutes as long as the chemotherapy cycle continues. Exercise on the cycle ergometer will begin with a 5-minute warm-up and will progress to 30 minutes of exercise at a speed corresponding to 40%-60% of the heart rate reserve calculated by the Karvonen formula [30]: (220 – age) – (heart rate of rest × % intensity) + resting heart rate. The exercise will end with 5 minutes of recovery. The objective will be to maintain the patient at a score of 12 for the perception of dyspnea and physical fatigue, as measured by the Borg scale [31] (12 indicates that the patient’s dyspnea and physical fatigue is above “relatively easy” and below “slightly tiring”), during exercise on the cycle ergometer. The Borg scale presents a range of scores from 6 (no effort) to 20 (maximum effort). Therefore, if the patient is considered fit by the physiotherapist, the speed on the cycle ergometer will be gradually increased until the patient reaches 60% of the heart rate reserve. We will record heart rate and peripheral oxygen saturation (Palmsat 2500 pulse oximeter; Nonin), dyspnea and physical fatigue (Borg scale) [28], and blood pressure (Premium Aneroid Sphygmomanometer and Littmann Classic II Stethoscope) before, during, and after each physical training protocol session. The session may be interrupted at any time if the patient presents signs or symptoms such as dizziness, dyspnea, fatigue, or nausea. If the patient requires any emergency assistance during the period in which they are undergoing physical training supervised by the study physiotherapist, the same physiotherapist will contact the medical team on duty responsible for the patient in the oncology ward to provide the necessary assistance to stabilize the condition of the patient. To assist in blinding the evaluator, a booklet titled “Why do I need to move when I am hospitalized” [32] will be given to patients in both groups. The cycle ergometer will always be removed from the patient’s room after the training session to ensure blind evaluation.

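### The training-harm question is tied to the next session, so it does not cover delayed effects of the last session and may not cover a session after which training stops

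*Protocol article*

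**What the plan says.** The Objective in the abstract and the end of the Introduction both list adverse effects of the training among the things to be evaluated.

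Assessments says how they are collected: through one question written by the researchers, "that will be answered every day before starting a new aerobic exercise session". Procedures gives the same trigger and adds the look-back: before the day's session "the patients will be asked if they feel any type of discomfort that is related to the previous day’s training", with muscle or joint pain in the legs as the example.

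Only one arm has sessions: "The patients allocated to the intervention group will participate in an aerobic training protocol on a cycle ergometer" (Interventions). The article describes the number of sessions in two ways. Procedures has "Aerobic training will be carried out from Monday to Friday while the patients are hospitalized for the chemotherapy cycle", while Interventions has "The training will be carried out with daily sessions for 4 days lasting 40 minutes as long as the chemotherapy cycle continues". Procedures also suspends exercise whenever chemotherapy is interrupted and restarts it when chemotherapy resumes.

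At the final assessment, on the day after the chemotherapy cycle ends, the patients' "subjective perception of satisfaction and discomfort in relation to the proposed protocol will be assessed through 2 questions", each scored 0 to 10 (Assessments). On analysis, Statistical Design says: "Descriptive analysis will be used for recruitment, completion, and adherence rates and potential adverse events".

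**The concern.** A question that is put before the next session, about the previous day's session, needs a next session in order to be asked. The last session never has one. Nor does the session after which a patient withdraws from training, or the session before a chemotherapy interruption from which training does not restart. If training does restart after a gap, the previous day had no training, so a literal reading of the look-back passes over the session before the gap. The same applies to a Friday session followed by a Monday question.

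Muscle and joint soreness, the article's own example, is the kind of effect that shows up the day after exercise, so it is what this gap loses. The gap is not neutral either. Where discomfort is the reason for stopping, the missing answer is the one most likely to be positive. A descriptive harm rate built on these answers would make the intervention look better tolerated than it was, and tolerability will matter to anyone deciding whether to adopt exercise on an oncology ward.

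**Working it through.** The plan states no figure for harms, so there is nothing to reproduce. The check is a count of coverage, followed by an illustration of what the gap does to incidence.

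**1. Coverage by session.** With *k* sessions, a question asked before each new session about the one before covers *k* − 1 sessions and leaves 1/*k* uncovered.

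- *k* = 4 (Interventions): 1/4 = 25% uncovered.
- *k* = 5 (Procedures, one Monday-to-Friday week): 1/5 = 20% uncovered.
- Stopped after two sessions: 1/2 = 50% uncovered.
- Stopped after one session: 1/1 = 100% uncovered.

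The last two assume that no question is put once training has stopped. The article does not fix the number of sessions per patient, so all four are examples.

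**2. Effect on patient-level incidence.** The documents give no risk of an adverse effect per session. Assume a constant risk *p*, independent between sessions, with full capture of earlier sessions and no capture of the last. True incidence is then 1 − (1 − *p*)^*k*, recorded incidence is 1 − (1 − *p*)^(*k*−1), and the shortfall is *p*(1 − *p*)^(*k*−1). Values of *p* from 5% to 20% are assumptions, chosen to show a range.

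| *k* | *p* = 5%: true / recorded | *p* = 10%: true / recorded | *p* = 20%: true / recorded |
|---|---|---|---|
| 2 | 9.8% / 5.0% | 19.0% / 10.0% | 36.0% / 20.0% |
| 4 | 18.5% / 14.3% | 34.4% / 27.1% | 59.0% / 48.8% |
| 5 | 22.6% / 18.5% | 41.0% / 34.4% | 67.2% / 59.0% |

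With four sessions the shortfall runs from 0.05 × 0.95³ = 0.043 to 0.20 × 0.80³ = 0.102, about 4 to 10 percentage points. With five it runs from 0.05 × 0.95⁴ = 0.041 to 0.20 × 0.80⁴ = 0.082, about 4 to 8 points.

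**3. Dependence on the denominator.** A rate per session asked about would not be biased under these assumptions, because the uncovered session leaves both numerator and denominator. It becomes biased once stopping depends on harm. Patient-level incidence is too low in either case.

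**4. Whether other sources close the gap.**

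- *In-session recordings* (Interventions): heart rate, saturation, Borg scores and blood pressure are taken around every session, including the last. They show acute reactions, not soreness the next day. A session may be stopped for symptoms, but the article does not say that the reason is logged as an adverse event.
- *Final 0-10 discomfort rating* (Assessments): one overall score for the protocol, with no event, type or date.
- *MSAS-BR* (Assessments): 32 symptoms over the previous week, pain among them, at the initial and final assessments in both arms. It gives symptom scores, not training-related events.
- *Record review* (Assessments): cardiac, pulmonary, infectious or neurological complications of chemotherapy, and intensive care transfer. Soreness from exercise falls outside these categories.

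Two of these sources need the patient to reach the final assessment. Participants excludes patients who are moved to intensive care or whose chemotherapy is discontinued, so some of them may not reach it.

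**The case against.** The strongest reply is that the trial does not depend on this one question. Every session is monitored, the discomfort rating follows soon after the end of training, and the MSAS-BR asks both arms about pain and other symptoms over a week that will normally include the last session. Statistical Design does not limit adverse events to answers given before a session. The article also condenses a longer protocol, which may hold fuller harm forms.

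Much of this stands, and it rules out three stronger readings that a reader might infer:

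- *That the last session, and patients who stop because of harm, are never counted.* The documents do not support this, because several other sources touch those patients. The physiotherapist may also come to the bedside, ask about yesterday and then hear the patient decline. Nothing says that such an answer would be discarded, so for stopped training the supportable wording is that the effect may be missed.
- *That a patient with one session yields no harm data.* In-session recordings exist for that session.
- *That there is no comparator.* The MSAS-BR is one, though an indirect one. Asking only exercisers about effects of exercise is natural for a descriptive objective, and the article promises no comparison of harms between arms.

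The reply does not remove the timing defect. The article states the collection rule twice and consistently, so this is a rule that is stated, not a detail left to a fuller document. None of the other sources gives an event count for the day after the last session.

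**Conclusion.** The point holds as a defect in the timing of one instrument. Taken as written, the dedicated question does not cover delayed effects of the last session, which is 25% of sessions on one stated schedule and 20% on the other. It may also fail to cover the session after which training stops or chemotherapy is interrupted. Patient-level incidence of training-related adverse effects is therefore biased downward.

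The coverage shares need only the session count. The loss of roughly 4 to 10 percentage points in incidence rests on the assumed 5% to 20% risk per session, on independence between sessions, and on the last session going wholly unrecorded. It shows the order of size and is not an estimate. The primary outcome, the sample size and the planned tests are unaffected.

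**What to change.** In the exercise arm, have the unblinded treating physiotherapist ask the same question on every day after a session, whether or not a new session takes place, and again on the final-assessment day. Word it to cover the time since the last session, which also deals with weekends and interruptions. Report the proportion of patients with at least one event among all who had at least one session.

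Procedures says that a blinded assessor collects all data. That sentence needs an exception here, since an answer about yesterday's training reveals the allocation.

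For background, use the MSAS-BR pain and symptom items already collected in both arms. A daily question in controls is optional: it would give a closer comparison, but an unblinded physiotherapist would be recording answers in both arms.

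Reconcile the session schedules in Procedures and Interventions, so that the expected number of questions per patient is known.

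The cost is one extra short question per patient at the end of training, plus one on each day when a session is skipped.
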